### Participant safety and reporting of adverse effects

Adverse effects with pantoprazole are generally mild and transient. In RCTs conducted outside of the ICU, 1–3% of participants reported GI disorders (constipation, diarrhea, nausea, vomiting, bloating, and discomfort), headache, skin reactions, and injection site reactions [21]. Critically ill patients are at high risk of serious adverse events and the usual approach of reporting all serious adverse events to participating centres’ Research Ethics Boards (REB) would result in large numbers of reports of events not related to the trial intervention, but rather reflect the underlying disease process or expected complications of critical illness [22]. The most likely adverse effects associated with stress ulcer prophylaxis and withholding stress ulcer prophylaxis are bleeding and nosocomial infection, both of which are captured as outcomes and thus not reported as serious adverse events. Only serious adverse events that might reasonably be a consequence of participation in the trial and are judged by the investigators not due to the underlying disease or expected complications of critical illness will be reported to Health Canada, our study’s Data Safety Monitoring Committee (DSMC) and the centre’s REB.

The DSMC will be composed of three to five members with experience and expertise in methods, statistics and pediatric critical care collectively. None of the members will be on the steering committee or otherwise involved in the trial to maintain their independence. The primary purpose of the DSMC is to ensure the safety of the children enrolled in the trial. The DSMC will also ensure the credibility of the trial and the validity of its results. The committee will meet and review the available data after 25 and 50% of the patients have been enrolled. Additional meetings may be held at the discretion of the Chair of the DSMC. The committee will receive SAE reports as they occur. All data will be presented to the DSMC tabulated by intervention group but the members will remain blinded to the actual group assignment. The committee will review serious adverse events and centre performance (enrollment, data quality and protocol adherence) and any pertinent external data such as newly published studies or other potentially relevant safety information. The committee will be advisory to the Steering Committee, making any recommendations regarding continuing or suspending the trial enrolment, or modifying trial protocol and procedures. They may recommend early termination of the trial if there are severe adverse events associated with the trial intervention, but no formal stopping rules will be used: this decision will be based on clinical judgment of the DSMC. The DSMC will keep all trial data, committee deliberations, and meeting minutes confidential until the end of the trial.

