### Blinding

Pantoprazole solution is clear and colourless. All clinicians, research staff, and parents and guardians will be unaware of the treatment allocation. Only the Research Pharmacist at each site will be aware of the treatment allocation. The group assignment will not be revealed upon request of the treating team as the treatment for adverse events and accidental overdoses is symptomatic and knowledge of the group assignment will not be clinically useful.

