## Discussion

Large RCTs are uncommon in pediatric critical care; only 10 trials randomizing more than 500 children have been published [13]. In addition, one-third of published trials are stopped early, most frequently for feasibility problems or futility [13]. Clearly a pilot trial is needed before undertaking such a trial in this relatively small, highly acute and heterogeneous population. Simply conducting a pilot trial will not guarantee the successful completion of a large trial; only 13% of pilot trials in pediatric critical care led to larger trials [25]. This pilot trial evaluates the important threats to the feasibility of a large RCT: screening, accrual, enrollment, and protocol adherence - with specific criteria for considering whether a trial is feasible. The number of participating PICUs in this study will help to ensure that the results are generalizable beyond a few highly-motivated centres.

This pilot trial may suggest that a larger trial is not feasible. It is more likely that this carefully designed pilot trial will ensure that the larger trial we undertake is successful. Within the Canadian Critical Care Trials Group, this programmatic approach has led to large, rigorous and practice-changing trials [26–29]. If the pilot trial leads to a conclusion that a larger trial is feasible, we will conduct a large multicentre trial focusing on clinical outcomes. We propose using the same inclusion and exclusion criteria, and intervention, but these may be modified based on the results of the pilot trial. The objective of the large trial is to determine if a strategy of withholding stress ulcer prophylaxis in critically ill children is not inferior to a strategy of routine stress ulcer prophylaxis. We hypothesize that withholding stress ulcer prophylaxis will not result in an unacceptable increase in upper GI bleeding. An important secondary hypothesis is that there will be fewer nosocomial infections (VAP and CDAD) in the group who do not receive prophylaxis. We will likely use a non-inferiority design because stress ulcer prophylaxis is already commonly used and we wish to test if withholding this conventional treatment results in an important increase in bleeding events. If the increase is small, it may be balanced by avoiding the adverse events and costs associated with prophylaxis which is almost universally administered to critically ill children today.

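### The DSMC is kept blind to group identity with no stated exception, so it could see an imbalance in harm without knowing which treatment it counts against (minor, cheap to fix)

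*Protocol article*

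**What the plan says.** Under Participant safety and reporting of adverse effects, the protocol article sets how data reach the committee: "All data will be presented to the DSMC tabulated by intervention group but the members will remain blinded to the actual group assignment". The Blinding section adds: "Only the Research Pharmacist at each site will be aware of the treatment allocation". Neither section gives an exception for the DSMC.

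The safety section makes the children's safety the committee's primary purpose. On stopping it says: "They may recommend early termination of the trial if there are severe adverse events associated with the trial intervention". There are no formal rules, and "this decision will be based on clinical judgment of the DSMC". The committee is also to review "any pertinent external data such as newly published studies or other potentially relevant safety information". Scheduled reviews fall after 25% and 50% of enrolment.

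On the harms themselves, the same section says the most likely adverse effects of giving or withholding prophylaxis "are bleeding and nosocomial infection, both of which are captured as outcomes and thus not reported as serious adverse events". The Discussion hypothesises that "there will be fewer nosocomial infections (VAP and CDAD) in the group who do not receive prophylaxis". It also allows for some increase in bleeding when prophylaxis is withheld: "If the increase is small, it may be balanced by avoiding the adverse events and costs associated with prophylaxis".

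**The concern.** The masking rule sits badly with the committee's task. Tables by Group A and Group B show whether the groups differ. They do not show whether pantoprazole or its absence is responsible, nor whether the direction agrees with a newly published trial.

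Direction matters more than usual here because the two main harms are expected on opposite sides. More bleeding on placebo would be the anticipated price of withholding prophylaxis, to be set against fewer infections. More bleeding on pantoprazole would be an unexpected harm with no such offset. The same masked table fits both readings.

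At stake is the quality of the committee's advice in the uncommon case of a worrying imbalance. Without the label it might suspend a pilot that could reasonably continue, or let one continue that should be paused. The validity of the feasibility results is not in question.

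**Working it through.** The point is mainly textual. The article gives no figure for what the DSMC will see, so there is none to reproduce. The arithmetic below only sizes the issue.

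**Inputs**
- 120 children, randomized 1:1 (Sample size justification; Allocation).
- Reviews at 25% and 50%: 0.25 × 120 = 30 and 0.50 × 120 = 60 children, about 15 and 30 per arm.
- Incidence of important bleeding 0.4% to 5% (Background), applied to both arms together, assuming complete follow-up at each review.
- No usable VAP or CDAD incidence is given, so expected infections cannot be computed.

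**Bleeds expected in total** (n × p; binomial probabilities)

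| Review | Incidence | Expected bleeds | P(no bleed) = (1 − p)^n | P(3 or more) |
|---|---|---|---|---|
| 30 children | 0.4% | 0.12 | 0.887 | 0.0002 |
| 30 children | 5% | 1.5 | 0.215 | 0.188 |
| 60 children | 0.4% | 0.24 | 0.786 | 0.0018 |
| 60 children | 5% | 3.0 | 0.046 | 0.583 |

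**What a masked split would look like.** Take three bleeds at the 50% review, the top of the expected range, all in one group (an assumed split): 3/30 v 0/30.
- Difference: 3/30 − 0/30 = 10 percentage points.
- Newcombe 95% CI: −3.1 to 25.6 points. Two-sided Fisher p = 0.24.
- Labels exchanged: −10 points, 95% CI −25.6 to 3.1.

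The table is inconclusive either way, but its sign, and so its clinical meaning, reverses with the label. If both arms truly bleed at 5%, a 3-to-0 split in one direction or the other has probability 2 × 0.127 × 0.215 = 0.055. At 0.4% it is about 0.0004.

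**Could the committee infer the label from the pattern?** Not reliably. The arm rates below are assumptions; the probabilities come from enumerating two independent binomials.

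| Assumed rates | Event expected in | P(that arm has more), 15 per arm | 30 per arm |
|---|---|---|---|
| Bleeding 5% placebo, 0.4% pantoprazole | placebo | 0.52 | 0.75 |
| VAP 10% placebo, 11.4% pantoprazole (10% × RR 1.14) | pantoprazole | 0.43 | 0.49 |
| VAP 10% placebo, 17.7% pantoprazole (10% × RR 1.77) | pantoprazole | 0.64 | 0.75 |

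The relative risks 1.14 and 1.77 are the estimate and upper confidence limit that the Background gives for VAP; the 10% base rate is assumed. With equal 5% bleeding rates, some imbalance still appears with probability 0.63 at 15 per arm and 0.75 at 30 per arm, equally likely in either direction.

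**The case against.** The strongest reply is that this is an unwritten exception and not an error. Masked A/B review is common DSMC practice. A right to unmask on request is the kind of detail that a charter holds, and a condensed article need not repeat it. The article describes how data are presented; it does not say that a DSMC request would be refused, whereas it says exactly that about the treating team. The sentence about pharmacists is in a section on trial conduct that does not mention the DSMC.

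This reduces the weight of the point but does not remove it. The article does not leave the matter open: it says flatly that members stay blinded. A charter that allowed unmasking would contradict that sentence, which is itself a reason to amend it. The reason given for refusing the treating team, that treatment is symptomatic, concerns the bedside care of one child and not a judgment of aggregate harm by arm.

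Three further objections bear on size, and they stand:
- The list of items the committee reviews names serious adverse events, centre performance and external data. Bleeding and infection reach it only if the phrase covering all data includes the clinical outcomes. That is an inference.
- The committee has other safeguards: serious adverse event reports as they occur, already screened for relation to the trial; extra meetings at the Chair's discretion; and freedom to recommend suspension on any imbalance or on a new publication alone.
- Events will be few, and learning the label on a 3-to-0 table would seldom change the advice.

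The Analysis and reporting section also plans blinded analysis and, if eligibility is not importantly changed, carries the pilot children into the large trial without unblinding. That is a good reason to keep masked review as the default. It is no reason to bar independent members, already bound to confidentiality, from the label when they judge that they need it.

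**Conclusion.** The concern holds, as a minor safety improvement. The stated rule keeps the DSMC blind to group identity with no exception, while the same section asks it to attribute harm to the intervention and to weigh outside evidence. Because the expected harms run in opposite directions, a masked imbalance cannot be read without the label, and the label cannot be reliably guessed at 15 or 30 children per arm.

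The practical size is small. The chance of three or more bleeds by the 50% review runs from 0.2% to 58% across the article's incidence range, and an imbalance serious enough to need the label would be rarer still. The bleeding argument assumes that those outcomes are in the committee's tables; the size for infection is unknown. Nothing in the feasibility results, the sample size or any error rate depends on this.

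**What to change.** In the safety section, replace the clause that keeps members blinded with wording such as: *as Group A and Group B; the DSMC may obtain the group identity at its own request, without disclosure to the Steering Committee, sites, adjudicators or analysts*. Add a matching exception to the sentence in the Blinding section on who knows the allocation. Masked review remains the default, and no stopping rule or numerical trigger is added.

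The cost is one sentence and one phrase, and the existing randomization schedule supplies the label. The downside is that the committee may occasionally be unmasked, which slightly weakens masked review. Clinicians, families, investigators, adjudicators and analysts stay blinded, so the plan to carry pilot patients into the large trial is preserved.

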### Analysis and reporting

All analyses will be performed without knowledge of group assignment and using an intention-to-treat principle. There will be no interim analyses for this pilot trial. For the feasibility outcomes we will report the proportions of children meeting each success criterion and the associated 95% confidence intervals. If, after the completion of the pilot trial, the study Steering Committee determines that there are no important changes to the inclusion and exclusion criteria, the results will not be unblinded for the clinical outcomes of the pilot trial. Instead, we will report the feasibility outcomes, present the clinical outcomes as a single cohort, and consider the pilot trial to be an internal pilot, meaning that we will include the pilot trial patients in the larger RCT. If the Steering Committee judges that a large trial is not feasible or if including the pilot trial patients in the larger RCT is inappropriate, the clinical outcomes will be reported by group so that the trial can be included in future meta-analyses. We will use the SPIRIT and CONSORT guidelines for reporting [23, 24].

## Discussion

Large RCTs are uncommon in pediatric critical care; only 10 trials randomizing more than 500 children have been published [13]. In addition, one-third of published trials are stopped early, most frequently for feasibility problems or futility [13]. Clearly a pilot trial is needed before undertaking such a trial in this relatively small, highly acute and heterogeneous population. Simply conducting a pilot trial will not guarantee the successful completion of a large trial; only 13% of pilot trials in pediatric critical care led to larger trials [25]. This pilot trial evaluates the important threats to the feasibility of a large RCT: screening, accrual, enrollment, and protocol adherence - with specific criteria for considering whether a trial is feasible. The number of participating PICUs in this study will help to ensure that the results are generalizable beyond a few highly-motivated centres.

This pilot trial may suggest that a larger trial is not feasible. It is more likely that this carefully designed pilot trial will ensure that the larger trial we undertake is successful. Within the Canadian Critical Care Trials Group, this programmatic approach has led to large, rigorous and practice-changing trials [26–29]. If the pilot trial leads to a conclusion that a larger trial is feasible, we will conduct a large multicentre trial focusing on clinical outcomes. We propose using the same inclusion and exclusion criteria, and intervention, but these may be modified based on the results of the pilot trial. The objective of the large trial is to determine if a strategy of withholding stress ulcer prophylaxis in critically ill children is not inferior to a strategy of routine stress ulcer prophylaxis. We hypothesize that withholding stress ulcer prophylaxis will not result in an unacceptable increase in upper GI bleeding. An important secondary hypothesis is that there will be fewer nosocomial infections (VAP and CDAD) in the group who do not receive prophylaxis. We will likely use a non-inferiority design because stress ulcer prophylaxis is already commonly used and we wish to test if withholding this conventional treatment results in an important increase in bleeding events. If the increase is small, it may be balanced by avoiding the adverse events and costs associated with prophylaxis which is almost universally administered to critically ill children today.

## Abbreviations

CCCTG: Canadian Critical Care Trials Group
CDAD: Clostridium difficile-associated diarrhea
CI: Confidence interval
DSMC: Data safety monitoring committee
GI: Gastrointestinal
H_2_RA: Histamine-2 receptor antagonist
PICU: Pediatric intensive care unit
PPI: Proton-pump inhibitor
RCT: Randomized controlled trial
REB: Research Ethics Board
RR: Relative risk
VAP: Ventilator associated pneumonia
